## Abstract

**Background:**

Among chronic diseases, cognitive, neurological, and cardiovascular impairments are becoming increasingly prevalent, generating a shift in health and social needs. Technology can create an ecosystem of care integrated with microtools based on biosensors for motion, location, voice, and expression detection that can help people with chronic diseases. A technological system capable of identifying symptoms, signs, or behavioral patterns could provide notification of the development of complications of disease. This would help the self-care of patients with chronic disease and save health care costs, promoting the autonomy and empowerment of patients and their caregivers, improving their quality of life (QoL), and providing health professionals with monitoring tools.

**Objective:**

The main objective of this study is to evaluate the effectiveness of a technological system (the TeNDER system) to improve quality of life in patients with chronic diseases: Alzheimer disease, Parkinson disease, and cardiovascular disease.

**Methods:**

A multicenter, randomized, parallel-group clinical trial will be conducted with a follow-up of 2 months. The scope of the study will be the primary care health centers of the Community of Madrid belonging to the Spanish public health system. The study population will be patients diagnosed with Parkinson disease, Alzheimer disease, and cardiovascular disease; their caregivers; and health professionals. The sample size will be 534 patients (380 in the intervention group). The intervention will consist of the use of the TeNDER system. The system will monitor the patients by means of biosensors, and their data will be integrated into the TeNDER app. With the information provided, the TeNDER system will generate health reports that can be consulted by patients, caregivers, and health professionals. Sociodemographic variables and technological affinity will be measured, as will views on the usability of and satisfaction with the TeNDER system. The dependent variable will be the mean difference in QoL score between the intervention and control groups at 2 months. To study the effectiveness of the TeNDER system in improving QoL in patients, an explanatory linear regression model will be constructed. All analyses will be performed with the 95% CI and robust estimators.

**Results:**

Ethics approval for this project was received on September 11, 2019. The trial was registered on August 14, 2020. Recruitment commenced in April 2021, and the expected results will be available during 2023 or 2024.

**Conclusions:**

This clinical trial among patients with highly prevalent chronic illnesses and the people most involved in their care will provide a more realistic view of the situation experienced by people with long-term illness and their support networks. The TeNDER system is in continuous development based on a study of the needs of the target population and on feedback during its use from the users: patients, caregivers, and primary care health professionals.

**Trial Registration:**

ClinicalTrials.gov NCT05681065; https://clinicaltrials.gov/ct2/show/NCT05681065

**International Registered Report Identifier (IRRID):**

DERR1-10.2196/47331

## Introduction

### Background

With the increase in population aging in Europe, chronic diseases are becoming more prevalent [1]. This reality represents a major challenge to health care systems due to comorbidities and outcomes such as increased dependency [2-4]. It is a priority to promote the autonomy and empowerment of patients and their caregivers, improve their quality of life (QoL), and provide tools enabling better monitoring by health professionals [5-7].

Among chronic diseases, cognitive, neurological, and cardiovascular impairments are becoming increasingly prevalent, generating a shift in health and social needs [8]. According to the World Health Organization (WHO) in a 2018 report, cognitive impairment and dementias, including Alzheimer disease (AD), remain one of the greatest global public health challenges facing our society [9]. The number of people worldwide living with a cognitive impairment such as dementia, is estimated at 44 million; this is expected to double by 2030 and is likely to increase to around 152 million by 2050. Among neurological disorders, Parkinson disease (PD) affects 1.2 million people in Europe [10]. Patients with PD, in addition to symptoms related to movement disorders, also develop cognitive impairment and emotional and behavioral disturbances that are important to follow closely [10]. Cardiovascular disease (CVD) accounted for 31% of all global deaths in 2016, and it is considered the leading cause of premature death (37% of all deaths under the age of 70) and disability in Europe and worldwide [11]. Early detection of disease progression and early treatment is essential [12].

Technology can create an ecosystem of care integrated with microtools based on biosensors for motion, location, voice, and expression detection that can help people with chronic diseases [13]. Today, these data streams, including sensor measurements, activity logs, and user-generated content, are used to measure or provide robust proxies for human behavior and function in both health and disease. This is called digital phenotyping [14].

Digital phenotyping is the in situ, moment-to-moment quantification of the human phenotype at the individual level using data from personal digital devices [15]. These microtools are able to recognize changes in a person’s habitual behaviors, movements, and mood through a multisensory system composed of smartphones, wearables, and other connected devices [16]. In addition, digital phenotyping allows the integration of an interactive communication service between health and social services, which can bring advantages in patient care and help detect risk situations, improving the autonomy of patients and the care they receive from caregivers and health professionals [17].

The development of a technological system capable of identifying symptoms, signs, or behavioral patterns that could provide alerts for the development of complications of these diseases would help the self-care of people with chronic diseases, their caregivers, and health professionals, as well as save costs for the health care system [18,19]. Some studies on digital phenotyping in patients with chronic disease have demonstrated its usefulness in treatment for mental health problems, diabetes, asthma, and CVD, showing positive effects on self-care and adherence to treatment [20,21]. This has been achieved by detecting clinical phenomena through digital tools that have enabled health professionals to adapt their assistance to the environment and characteristics of patients [21].

Until now, research on digital phenotyping has been led and developed by teams specialized in the technological field. As suggested by Huckvale et al [20], these challenges must be addressed under a multifaceted and multidisciplinary perspective involving health professionals and users in the development of such technological systems.

Needs such as the detection of behavioral changes in patients with dementia, gait changes and fall prevention in patients with PD, and the close monitoring of risk factors for CVD could be covered by intelligent monitoring system [19]. This would help the self-care of patients with chronic diseases, promoting the autonomy and empowerment of patients and their caregivers and improving their QoL.

### Objectives

The main objective of this study is to evaluate the effectiveness of a technological system (the TeNDER system) to improve QoL in patients with chronic diseases, including AD, PD, and CVD.

The secondary objectives are (1) to describe the satisfaction of patients, caregivers, and health professionals with the TeNDER system; (2) to describe the characteristics of the usability of the TeNDER system from the perspective of its potential users; and (3) to explore whether the use of the TeNDER system increases caregivers’ perceived satisfaction with the care provided and, in relation to this, improves their QoL.

## Methods

### Design

A multicenter, randomized, parallel-group clinical trial will be conducted with a follow-up of 2 months. The unit of randomization will be the patient.

This study protocol is part of a proposal with European funding under the European Union’s Horizon 2020 Research and Innovation Programme (grant 875325). The European consortium that developed the proposal is composed of different countries: Spain, Portugal, Italy, Slovenia, Greece, Germany, and Belgium [22].

The TeNDER project is developed in 4 European countries (Spain, Germany, Italy, and Slovenia). To account for the differences in the health systems of the participating countries and organizations, this research protocol refers to the primary care health centers (PCHCs) of the Madrid Health Service, which belongs to the Spanish public health system.

The TeNDER project brings together experts in technological development and users, including chronic patients, their caregivers, and primary care health professionals (PCHPs). Therefore, it will have an initial phase of cocreation in which the needs of the users will be explored. Based on the results, the technical team will work on improving and adapting the TeNDER system.

### Study Population

The TeNDER project will include patients diagnosed with at least one of the following chronic conditions: PD, AD, other dementias, and CVD. Along with the patients, their caregivers, and their health professionals from the PCHCs will also be included as participants.

All participants must accept and sign the informed consent form. If a patient does not have the capacity to do so, a family member will sign the form on their behalf.

### General Inclusion Criteria for Patients

Patients will be included if they are older than 60 years at follow-up, are referred by a PCHP at the PCHC, and are able to understand the local language. If a patient is dependent on others, they must have a caregiver or other responsible party.

### General Exclusion Criteria for Patients

Patient who according to the judgment of their caregiver or PCHP are unable to follow the requirements of the study (eg, patients with inability to move or move around at home) or who have a life expectancy of less than 6 months will be excluded.

### Specific Criteria for Patients With Each Chronic Illness

Patients with PD must have a confirmed diagnosis. Patients with AD must have a Mini Mental State Examination score between 19 and 28 points. Patients with a Global Deterioration Scale over 6 or 7 will be excluded. Patients with CVD will include those with the following conditions: heart failure with NYHA (New York Heart Association) Scale grade II to III heart function, and stable coronary artery disease or artery coronary disease with or without ST-elevation, atrial fibrillation, pacemaker, and stroke. Patients with arterial coronary disease that occurred less than 4 weeks ago or with severe aortic stenosis will be excluded.

### Inclusion Criteria for Caregivers

Caregivers of the selected patients who are aware of the patient’s health and social situation and who provide direct care or support for daily activities will be included. In addition, caregivers must be able to use a smartphone.

### Exclusion Criteria for Caregivers

Caregivers will be excluded if they do not understand the local language.

### Inclusion Criteria for PCHPs

Medical doctors and nurses attending the adult population of the participating PCHC will be included. They must carry out their professional activity in a PCHC that participates in the study and have at least one year of professional experience. They should be able to provide continuity of care for the patient during the intervention.

No exclusion criteria were applied for the PCHPs.

### Sample Size

The European consortium that developed the proposal called for a sample size of 1766 patients (1031 in the control group and 735 in the intervention group) with the aim of using the TeNDER system to achieve an improvement in QoL, as measured by the Short Form–36 Health Survey (SF36) [23], of 6 points in the intervention group as compared to the control group.

According to previous studies, the SD for QoL score in the population with the chronic diseases under study (PD, AD, and CVD) ranges between 16 and 27 [23-25]. For the power calculation, we used the highest value of this SD. Therefore, the sample size will allow a power of 98.8% to detect ≥6 differences in the overall score of the SF36 questionnaire, if they exist. Calculations were performed with Epidat (version 4.2; Xunta de Galicia).

In the PCHC of the Madrid Health Service, as part of the European consortium, 534 patients will be included (380 in the intervention group and 254 in the control group). No differentiation by pathology will be established.

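### The only stated power, 98.8%, goes with the 1766-patient consortium; at the SD the protocol says it used (27), the Madrid trial it describes has about 64% to 78%

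*Protocol article*

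**What the plan says.** The Sample Size section opens with the consortium, which called for a "sample size of 1766 patients (1031 in the control group and 735 in the intervention group"), aiming at an SF36 improvement "of 6 points in the intervention group as compared to the control group". It reports that the SD in these diseases "ranges between 16 and 27" and continues: "For the power calculation, we used the highest value of this SD". It then concludes that "the sample size will allow a power of 98.8"% to detect a difference of 6 points or more.

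Only after that does it turn to Madrid, as part of the consortium: "534 patients will be included (380 in the intervention group and 254 in the control group"). No power is attached to these numbers, and no other power figure appears in the article.

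Elsewhere the article is about Madrid. The Design section says that "this research protocol refers to the primary care health centers (PCHCs) of the Madrid Health Service". The Methods part of the abstract says: "The sample size will be 534 patients (380 in the intervention group"). The Recruitment and Randomization sections describe Madrid centers and central assignment by the Madrid research support unit. The Data Analysis and Statistical Plan section compares the two arms at 2 months, with robust estimators because patients are grouped by health center. It mentions neither pooling with other countries nor a country term.

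**The concern.** A power figure is useful only if it belongs to the analysis that will be reported. Here the sole figure goes with a sample roughly three times as large as Madrid's (1766 against 534 or 634), while the analysis section describes only the Madrid comparison. A reader who takes 98.8% as the power of this trial would think a true 6-point effect had a 1.2% chance of being missed. If Madrid then found no significant difference, the result could be read as strong evidence against a 6-point benefit. At the protocol's own SD, the Madrid sample would not support that reading.

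**Working it through.** **Inputs**
- Difference 6 points; SD 27 (highest of the range 16 to 27): Sample Size section.
- Consortium arms 1031 and 735: Sample Size section.
- Madrid: total 534, arms 380 and 254: Sample Size section. The abstract also gives 534 with 380 in the intervention group.
- Two-sided 5% level: an assumption. The Sample Size section gives no level; the analysis section uses 95% CIs and a 2-tailed t test.

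**Formula** (two independent means, normal approximation)

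SE = SD × √(1/n₁ + 1/n₂); power = Φ(6/SE − 1.96).

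**Step 1: the plan's own figure.** For 1031/735 at SD 27:

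SE = 27 × √(1/1031 + 1/735) = 1.303; 6/1.303 = 4.603; power = Φ(2.643) = 99.6%.

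This is 0.8 percentage points above the stated 98.8%, so the stated figure fits the consortium sample.

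**Step 2: which Madrid sample?** 380 + 254 = 634, not 534. If 534 and 380 are right, the control arm is 534 − 380 = 154. If 534 and 254 are right, the intervention arm is 534 − 254 = 280. If both arms are right, the total is 634. The document does not settle which, so all three are carried forward.

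**Step 3: Madrid power at SD 27**

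| Intervention/control | Total | SE | 6/SE | Power | Chance of missing 6 points |
|---|---|---|---|---|---|
| 380/254 | 634 | 2.188 | 2.742 | Φ(0.782) = 78.3% | 21.7% |
| 280/254 | 534 | 2.340 | 2.565 | Φ(0.605) = 72.7% | 27.3% |
| 380/154 | 534 | 2.579 | 2.326 | Φ(0.366) = 64.3% | 35.7% |

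A noncentral t calculation gives 78.2%, 72.6% and 64.1%. Even an equal split of 534 (267/267) gives only 72.8%. At the 380:254 ratio, 80% power at SD 27 would take about 266 controls and 398 intervention patients, 664 in all.

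**Step 4: the rest of the stated SD range**

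| Arms | SD 16 | SD 21.5 (midpoint) | SD 27 |
|---|---|---|---|
| 380/254 | 99.6% | 93.1% | 78.3% |
| 280/254 | 99.1% | 89.6% | 72.7% |
| 380/154 | 97.5% | 83.2% | 64.3% |

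With 380/254, Madrid reaches 98.8% only if the SD is about 17.6 or less. With 380/154, the SD would have to be about 14.9 or less, which is below the stated range.

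None of these figures allows for loss to follow-up or clustering. Either would lower them.

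**The case against.** The best defence is that the article does not misattribute anything. The 98.8% comes straight after the 1766 patients, and Madrid's numbers come later, introduced as a share of the consortium. This stands: a reader might infer that the protocol claims 98.8% for Madrid, and the order of the text does not support that. The fault is that the only power given does not belong to the trial described. If the consortium analysis is the one that counts, the article needs to say so, and it does not.

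Second, SD 27 is a deliberately cautious choice. It is tempting to say that Madrid is simply underpowered, with a real risk of 22% to 36% of missing the effect. That is too strong. The risk holds at the top of the SD range; at the midpoint, power is 83% to 93%, and at the bottom it is close to the stated figure. Much of the spread from 64% to 78% comes from the arm-size contradiction. But SD 27 is the value the protocol says it used, so its power statement has to be judged there first.

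Third, a reader might conclude from 98.8% against 99.6% that the consortium calculation is wrong. The gap is trivial. An assumed loss of about 16% would account for it: SE = 1.303/√0.84 = 1.422, power = Φ(6/1.422 − 1.96) = 98.8%. The document states no such loss, but nothing shows an error.

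Finally, a condensed article may leave details to a fuller plan, and the reported confidence interval will show the precision of a null result. Both are fair and limit the harm. Neither removes the problem of a printed power figure that does not apply to the sample printed beside it.

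**Conclusion.** The point holds in a limited form. The stated 98.8% fits the consortium sample and not the Madrid trial that the article describes. At SD 27 and 6 points, Madrid power is about 78% (380/254), 73% (280/254) or 64% (380/154). It is below 80% on every reading of the arm sizes. At SD 16 it is 97.5% to 99.6%. These results rest on an assumed two-sided 5% level, complete follow-up and no clustering. They do not show that Madrid will be underpowered, since that depends on the true SD, nor that the consortium power was miscalculated. The article does need correcting, because it defines a Madrid analysis and leaves the reader only a power figure for a different, much larger sample.

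**What to change.** 1. Reconcile the Madrid total with its arms (534 against 380 + 254 = 634) in both the abstract and the Sample Size section.
2. State the power of the Madrid comparison with the reconciled arms for SDs from 16 to 27, and name the significance level and sidedness.
3. Label 98.8% as applying only to the pooled consortium sample of 1766.
4. Alternatively to steps 2 and 3, if the pooled consortium analysis is the confirmatory one, say so explicitly and describe the Madrid results as part of it. Step 1 is needed either way.

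The change is to text only. The cost is a less favourable stated power at SD 27. No extra patients are needed, and the design, recruitment and analysis stay as they are.

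### The Madrid arm sizes (380 + 254 = 634) do not add up to the stated total of 534, so the total, the control arm and the allocation ratio cannot be determined

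*Protocol article*

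**What the plan says.** The Sample Size section of the protocol article gives two sets of numbers.

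- For the consortium: "a sample size of 1766 patients (1031 in the control group and 735 in the intervention group"). The target is an SF36 improvement "of 6 points in the intervention group as compared to the control group". The SD "ranges between 16 and 27", and "For the power calculation, we used the highest value of this SD". From this the section concludes that "the sample size will allow a power of 98.8% to detect ≥6 differences in the overall score of the SF36 questionnaire".
- For the Madrid centres: "534 patients will be included (380 in the intervention group and 254 in the control group").

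The Abstract (Methods) states: "The sample size will be 534 patients (380 in the intervention group"). It gives no control figure.

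The Recruitment section expects 84 participating professionals, each recruiting 8 patients. The Randomization section says that patients are randomised by pathology and assigned centrally, and gives no allocation ratio.

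**The concern.** The Madrid total and its two arms describe the same patients in one sentence, and they disagree. Dropout, rounding or the choice of power formula cannot explain a sum that fails, so at least one of the three numbers is wrong.

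The planned total, the size of each arm and the allocation ratio are basic design parameters. They set when recruitment is complete, how the central unit builds its allocation, and how many patients have to be fitted with the system. They are also the reference against which a reader will judge whether the trial reached its planned size. With two totals 100 patients apart, that judgement cannot be made from the article.

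**Working it through.** **Inputs.** From Sample Size: Madrid 534 in total, 380 intervention, 254 control; consortium 1766 in total, 1031 control, 735 intervention; difference 6 points; SD 16 to 27, with 27 used. From the Abstract: 534 in total, 380 intervention. From Recruitment: 84 professionals, 8 patients each. The significance level of the power calculation is not stated. I assume 5% from the 95% CIs, two-sided because the Data Analysis section specifies a 2-tailed *t* test.

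**1. Sums.**

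- Consortium: 1031 + 735 = 1766. This agrees with the stated total.
- Madrid: 380 + 254 = 634, against 534 stated. The gap is 100, and 100/534 = 18.7%.

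The fault is therefore confined to the Madrid figures.

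**2. Readings that change one number and keep the printed labels.**

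| Number changed | Intervention | Control | Total | Ratio, intervention:control |
|---|---|---|---|---|
| Total | 380 | 254 | 634 | 380/254 = 1.50 |
| Control arm | 380 | 534 − 380 = 154 | 534 | 380/154 = 2.47 |
| Intervention arm | 534 − 254 = 280 | 254 | 534 | 280/254 = 1.10 |

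The control arm is 254 or 154. Each reading is a slip of one in the hundreds digit, so the form of the error does not favour any of them.

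**3. Does recruitment settle it?** 84 × 8 = 672. This exceeds 634 by 38 and 534 by 138. It matches neither total and says nothing about the arms.

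**4. The protocol's own power figure.** SE = SD × √(1/n₁ + 1/n₂), and power ≈ Φ(6/SE − 1.96).

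For the consortium, SE = 27 × √(1/1031 + 1/735) = 1.30 and 6/SE = 4.60, so power = Φ(2.64) = 99.6%. The stated 98.8% is close, so it belongs to the 1766-patient sample. It is not a Madrid figure.

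**5. Illustration for Madrid alone, by the same formula.**

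| Intervention/control | SE at SD 27 | Power at SD 27 | Power at SD 16 |
|---|---|---|---|
| 380/254 | 2.19 | 78.3% | 99.6% |
| 380/154 | 2.58 | 64.3% | 97.5% |
| 280/254 | 2.34 | 72.7% | 99.1% |

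At SD 27 the choice of reading moves power by 78.3 − 64.3 = 14.0 percentage points. At SD 16 it moves it by 99.6 − 97.5 = 2.1 points. None of these figures allows for clustering by health centre.

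**6. Direction of allocation.** The control share is 1031/1766 = 58.4% in the consortium. In Madrid it is 254/634 = 40.1%, 154/534 = 28.8% or 254/534 = 47.6%. Madrid has the larger intervention arm under every reading, and the article gives no reason.

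**The case against.** The failed sum cannot be defended, but several things that might be built on it can be challenged.

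- **The readings are not equally supported.** The figures 534 and 380 each appear twice, in the Abstract and in Sample Size, while 254 appears once. The reading 380/154 needs one correction in one place; each of the others needs the same error in two places. This stands as a pointer, but it does not settle the matter, because the Abstract may simply have been taken from the Methods text.
- **The reversed split might be read as a second error, or as a sign that the arm labels were swapped.** The documents do not support either. Madrid is one part of a multi-country project, and nothing requires each part to follow the overall ratio. If Madrid's 380/254 lies within the 1766, the other sites would hold 1031 − 254 = 777 controls and 735 − 380 = 355 intervention patients, which is feasible. Both places attach 380 to the intervention group, and swapping the labels still gives 634. A control arm of 280 or 380 would need such a swap, so neither belongs among the readings.
- **The power figures might be read as contradicting the 98.8%.** They do not. That figure is claimed for the consortium sample and approximately reproduces there. SD 27 is the protocol's own choice, but it is the upper end of its range; at SD 16 power is above 97% under every reading.
- **The error may exist only in the article.** Assignment is central, recruitment began in April 2021, and the randomisation specification is not shown. A reporting slip fits the text as well as a flaw in the conduct of the trial. This limits what can be said about consequences; it does not remove the contradiction.

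**Conclusion.** The point holds in this form: the Madrid sample size is wrong as written. The arms sum to 634 against a stated 534, a gap of 100 patients or 18.7%, and the Abstract carries the same total. If the printed labels are right and only one number is wrong, the control arm is 254 or 154, the total is 634 or 534, and the allocation ratio is 1.50:1, 2.47:1 or 1.10:1. The figures are stated rather than absent; what the text does not allow is choosing between them.

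The arithmetic rests on no assumption. The power comparison does: it assumes a two-sided 5% level and SD 27, ignores clustering, and illustrates a Madrid-only analysis for which the protocol makes no power claim. The documents do not show that recruitment or randomisation actually followed conflicting numbers, and the reversed allocation is an unexplained observation, not a defect.

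**What to change.** Check the Madrid figures against the consortium allocation and settle one set: total, number per arm and allocation ratio. State that set identically in the Sample Size section and the Abstract, and confirm that the central unit's randomisation specification agrees. While doing so, confirm that Madrid's larger intervention arm is intended, and say so in one sentence.

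The cost is a text correction in two places and one check of the randomisation specification. The correction does not in itself call for additional patients.
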